### Retention

Adherence and retention in BE WELL is expected to be fostered by: 1) selection/retention of qualified staff, their training, and systematic quality control; 2) the relationship between staff and participants, 3) willingness to accommodate participant schedules and needs, and 4) resourcefulness and persistence of the staff. For purposes of follow-up assessment, a participant tracking database will be used to assure that participants are contacted on a timely basis. Subjects' contact information will be kept current and at least two alternative contacts will be collected. Subjects will be given a nominal payment for each data collection visit. Assessment staff, who will be blinded to treatment assignment, will contact subjects who miss a visit to reschedule the visit and to re-engage them in subsequent follow-ups. Subjects will be educated about the importance of follow-up assessment even if they are not adhering to the treatment. Priorities will be given to the primary and main secondary outcomes in cases where not all follow-up measurements may be obtained from a subject.

Ongoing monitoring of indices of participation in intervention activities helps interventionists identify participants who are having problems adhering to the intervention protocol and thus initiate recovery efforts. Such efforts can range from brief telephone discussion to an individual counseling session with the interventionist in which the participant who makes a decision to discontinue intervention can review concerns regarding BE WELL, reasons for staying in the study, and decisions about remaining a participant. Unless the participant declines, the interventionist will continue to contact the participant on a progressively less frequent schedule, starting monthly and decreasing to semi-annually to remind her/him of the opportunity to re-enter BE WELL.

### Sample size consideration and statistical analysis

#### Sample Size

In the only RCT conducted to date of lifestyle-induced (by caloric restriction and behavior change) weight loss for the management of asthma, effect size (Cohen's d) estimates ranged between 0.4 and 0.6 for various asthma symptom and lung function outcomes over a 12-month follow-up period [26]. A sample size of 324 is sufficient to detect an effect size of 0.4 between the WL and UC arms for 90% power at 5% alpha 2-sided, assuming up to a 20% loss to 12-month follow-up (or an end-of-the-study sample size of 259). The power estimate was calculated based on an independent t-test using simplified assumptions. Note that the t-test calculation is conservative because it does not account for variance reduction due to adjustment for repeated measures, nor for the better than chance comparability of the experimental groups.

#### Statistical analysis

The primary hypothesis compares Juniper ACQ scores between the WL and UC arms at 12 months using an intent-to-treat analysis. Linear mixed modeling, using SAS PROC MIXED [67] will test time and group interactions to assess whether within-subject change in Juniper ACQ scores differs by condition (equation 3).(3)

Due to randomization, the distributions of baseline values on the dependent variable (Y_0_) and baseline covariates (X_i _where i = 1 to k) should be similar between treatment arms and thus not bias the analysis. Nonetheless, to the extent they are associated with the outcome, their inclusion in the model will account for otherwise unexplained variation and hence increase the efficiency of the analysis. In addition, their inclusion will guard against imbalance in the distributions of these covariates between treatment arms, which can still occur despite randomization. a, g, and δ represent the random effects caused by clustering of patients with physicians and, in turn, physicians within clinics, and by blocking of patients within medical centers. ε takes into account the correlation of repeated measures within subjects.

The same analysis strategy is appropriate for evaluating secondary aims where the hypotheses are identical but with different outcome measures (e.g., lung function, asthma-specific QoL, asthma-related HCU). The longitudinal effects of the intervention will be assessed using the same model, except that the focus is comparisons within the intervention arm at different time points. Analyses will also be conducted to examine whether there is a dose-response relationship between intervention adherence and outcome, where dose is defined in terms of number of group sessions attended, number of self-monitoring logs kept, average daily intakes of calories and fat, and average number of minutes of physical activity per week.

The primary analyses will be intention-to-treat. Secondary per-protocol or as-treated analyses will be performed to help elucidate the primary findings. For subjects with missing data at follow-up, we will conduct and report on sensitivity analyses in which several previously recommended approaches for handling missing data in longitudinal trials will be used, e.g., multiple imputation and the pattern-mixture model [68].

We will use the MacArthur approach, which modified the Baron & Kenny criteria, for defining moderators and mediators in clinical research studies [69]. Let T be the treatment, M be the potential moderator or mediator, and O be the outcome. Association between T, M, and O is examined using the following models:(4)

M can be considered a mediator of the effect of T on O if T precedes M, γ1 ≠ 0, and either β2 ≠ 0 or β3 ≠ 0. M is a moderator of the effect of T on O if M precedes T, γ1 = 0, and β3 ≠ 0.

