## Aims

The BE WELL (*B*reathe *E*asier through *We*ight *L*oss *L*ifestyle) intervention trial was designed to address the gap in knowledge of whether weight loss improves asthma control. It aims to evaluate the efficacy of an evidence-based, comprehensive weight loss lifestyle intervention as adjunct therapy to usual care in the management of asthma in obese adults. The primary hypothesis is that compared with participants in the usual care (UC) arm, those in the weight loss intervention (WL) arm will achieve greater improvement in asthma control, as measured by a validated composite measure, the Juniper Asthma Control Questionnaire (ACQ) [28], at 12 months follow-up. Secondary aims include comparing the WL and UC arms on changes in ACQ scores at six months and in lung function, asthma-specific quality of life (QoL), asthma medication use, and asthma-related health care utilization (HCU) at six and 12 months. Potential mediators (e.g. weight loss and change in physical activity level and diet composition) and moderators (e.g., socio-demographic characteristics and comorbidities) of the intervention effects will be explored.

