### Baseline and Follow-up Measures and Data Collection

Table 2 shows the study measures and data collection schedule. In addition to the screening and baseline data collection activities described previously, follow-up visits for questionnaires, clinical measurements, and adverse event monitoring will be conducted at six and 12 months after randomization.

**Table 2 T2:** List of measures and data collection schedule

	Baseline	Follow-up month	
		
		6	12

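### The primary hypothesis is the 12-month difference in ACQ between arms, but the only test named is a time-by-group interaction, which with baseline ACQ as a covariate would measure something else

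*Protocol article*

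**What the plan says.** All references are to the protocol article.

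- **Hypothesis (Statistical analysis).** "The primary hypothesis compares Juniper ACQ scores between the WL and UC arms at 12 months using an intent-to-treat analysis". The Aims section also sets the primary hypothesis at 12 months and ranks the earlier visit lower: "Secondary aims include comparing the WL and UC arms on changes in ACQ scores at six months".
- **Test (Statistical analysis).** The linear mixed model "will test time and group interactions to assess whether within-subject change in Juniper ACQ scores differs by condition". No other test, coefficient or contrast is named for the primary outcome.
- **Baseline ACQ (Statistical analysis).** The baseline value of the outcome, Y_0, is listed with the baseline covariates, and "their inclusion in the model will account for otherwise unexplained variation and hence increase the efficiency of the analysis". The residual term "takes into account the correlation of repeated measures within subjects".
- **Visits (Baseline and Follow-up Measures and Data Collection).** Follow-up visits "will be conducted at six and 12 months after randomization". Table 2 lists the ACQ at baseline and at those two visits.
- **Power (Sample Size).** "The power estimate was calculated based on an independent t-test using simplified assumptions". The target is an effect size of 0.4 with 90% power at two-sided 5%, with 324 randomized and 259 remaining after 20% loss.

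**The concern.** A group-by-time interaction answers the 12-month question only under some codings of the model. When baseline is a covariate and the responses are two follow-up visits, the interaction asks whether the treatment effect changed between those visits. It does not ask whether there is an effect at the second one.

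The intervention makes this distinction matter. Table 3 places active weight loss in months 1 to 6 and gives months 7 to 12 the goal of holding the weight or continuing to lose slowly. A benefit that is largely present at month 6 and persists to month 12 is therefore a plausible form of success. An interaction between months 6 and 12 would be close to zero in that case, and a working intervention could be reported as having no effect on the primary outcome.

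**Working it through.** **Inputs from the protocol.** Effect size 0.4, two-sided alpha 5%, 1:1 allocation, 259 completers (taken as 130 and 129), follow-up ACQ at months 6 and 12.

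**Assumptions.** ACQ is scaled to SD 1 at each visit. Any two visits have the same correlation rho. The documents give no rho, so 0.3, 0.5 and 0.7 are shown. Powers use the noncentral t distribution.

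**Step 1: the plan's own figure.** 324 × 0.8 = 259.2, hence 259 completers. The standard error of a difference in means is √(1/130 + 1/129) = 0.1243. The noncentrality is 0.4 / 0.1243 = 3.22, and the power is 89.4%. The stated 90% is reproduced for a two-sample comparison at 12 months.

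**Step 2: Y_0 as covariate, responses at months 6 and 12, interaction as the test.** Let d6 and d12 be the WL-UC effects in SD units.

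- Interaction = d12 − d6.
- The SD of the within-person difference between visits is √(2(1 − rho)). With equal correlations, adjusting for baseline leaves this unchanged.
- Noncentrality = (d12 − d6) / [√(2(1 − rho)) × 0.1243].

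Worked case: d6 = 0.2, d12 = 0.4, rho = 0.5. The SD is 1.00, the noncentrality is 0.2 / 0.1243 = 1.61, and the power is 36%.

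| True effect (month 6, month 12) | rho 0.3 | rho 0.5 | rho 0.7 |
|---|---|---|---|
| 0.4, 0.4 | 5% | 5% | 5% |
| 0.3, 0.4 | 10% | 13% | 18% |
| 0.2, 0.4 | 27% | 36% | 54% |

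The first row is the type I error rate, because the tested quantity is exactly zero. A simulation of 4,000 trials gave 4.9% at rho 0.5 and 4.8% at rho 0.7.

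**Step 3: baseline as a response, categorical time, group-by-month-12 term only.** This term is the between-arm difference in change from baseline to month 12. Noncentrality = 0.4 / [√(2(1 − rho)) × 0.1243]. Power is 77%, 89% and 99% at rho 0.3, 0.5 and 0.7 (simulation 90.0% at 0.5 and 98.5% at 0.7). A sustained benefit is not missed.

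**Step 4: Y_0 as covariate, explicit WL-minus-UC contrast at month 12.** The residual SD is √(1 − rho²), which is 0.954, 0.866 and 0.714. Noncentrality = 0.4 / [√(1 − rho²) × 0.1243] = 3.37, 3.72 and 4.51. Power is 92%, 96% and 99% (simulation 95.9% at 0.5 and 99.3% at 0.7).

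So for one true pattern, 0.4 SD at both visits, the power is 5%, 77% to 99%, or 92% to 99%, depending on how the sentence about interactions is read.

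**The case against.** The strongest reply is that the model is defined by equation 3, which cannot be read in the text available here. It may show which visits are responses, how time is coded and which term is tested, and its absence from this copy is no fault of the plan. The section also opens by naming the 12-month comparison, the test sentence speaks of within-subject change by arm, and the Aims speak of improvement. All of this fits a model with baseline as a response and a month-12 interaction term, which would be a valid test (step 3). It equally fits a month-12 contrast drawn from a model with Y_0 as covariate (step 4). The article is also condensed, and software statements and covariance structure belong in an analysis plan.

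Much of this stands, and it rules out three stronger readings that a reader might infer:

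- **That the plan does not test the 12-month difference.** This is not established. Two ordinary readings do test it.
- **That an effect seen only at month 6 could be declared a 12-month success.** This would need a joint test over both follow-up visits with baseline as a response. The protocol mentions no such test, and it makes the six-month comparison secondary.
- **That the sample size or its 90% power is wrong.** Step 1 reproduces it for the 12-month comparison.

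What the reply does not remove is the wording itself. The readable text puts Y_0 on the predictor side and names the interaction as the test. Using baseline as a response as well would sit awkwardly with Y_0 as a covariate. Each reading that rescues the test relies on a term or contrast that the text does not name. This goes beyond detail left to an analysis plan, because the article does state the test.

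**Conclusion.** The concern holds as a mismatch between the primary hypothesis and the only test stated for it. It is not proof that the wrong parameter will be analysed. If baseline ACQ is a covariate and months 6 and 12 are the responses, as the wording implies, the stated interaction has 5% power for a sustained 0.4 SD benefit and 27% to 54% for 0.2 SD growing to 0.4 SD, against 89% for the comparison used to size the trial. The 5% figure does not depend on the correlation but does require equal effects at the two visits. The other figures rest on the assumed correlation of 0.3 to 0.7, equal SDs and 259 completers. If baseline is a response, the hypothesis is answered only by the single month-12 term, which remains to be named. The point deserves correction because the literal test can give the wrong decision on the primary outcome and the remedy costs almost nothing.

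**What to change.** In Statistical analysis, state that:

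1. Y_0 enters as a covariate and the ACQ scores at months 6 and 12 are the responses.
2. The primary test is the single-degree-of-freedom, baseline-adjusted WL-minus-UC contrast at month 12 from the planned mixed model, with its stated covariates and random effects kept.
3. The month-6 contrast is secondary, and the time-by-group interaction is descriptive.

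Equation 3 should be checked against this wording. The cost is a sentence or two of text and one contrast statement in the analysis program. No new data and no change to the sample size are needed.

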### Randomization and Blinding

Following BV2, participants will be randomized in a 1:1 ratio to the WL or UC arm. By applying a balance algorithm that originated in cluster randomized trials [29], BE WELL randomization will assure very close balance at baseline on age, sex, race/ethnicity, BMI and ACQ score stratified by participating KPNC medical centers, and better than chance balance on characteristics correlated with the balancing variables. Within each medical center, participants will be randomized in blocks to take advantage of complete data on baseline covariates across the recruited sample prior to randomization.

For the first block within a medical center, the imbalance scores of all possible allocations with equal numbers of participants between two anonymous groups (1 and 2) will be calculated using equation 1. The correspondence of groups 1 and 2 with either the WL or UC arm will be assigned randomly at the outset and used consistently throughout the trial.(1)

where k is the kth balancing factor (k = 1 to 5) as listed above;  and  are the average of kth factor for groups 1 and 2, respectively; and the weights (w) determine the relative contribution of each balancing factor to the imbalance B [30]. In BE WELL, equal weights will be assumed for all balancing factors. For categorical factors, orthogonal dummy variables, which identify individual factor levels, will be coded before imbalance score calculation. A set of optimal allocations will be determined by the lowest 1,000 calculated B values [30]. One allocation will be randomly selected from the set of optimal allocations for the block of participants about to be randomized.

After randomization of the first block of participants within a medical center, allocations for each subsequent block will be conditional on the chosen allocations of participants in earlier blocks. The imbalance score B for a new block will be computed using equation 2.(2)

where n_1 _is the number of participants in the existing block(s) and n_2 _is the total number of participants with the addition of the new block; *x*_1*ik *_and *x*_2*ik *_represent the kth factor of ith participant allocated in group 1 or 2. The process of sampling from the 1,000 lowest calculated B values will be repeated for all subsequent blocks.

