##### Intensive Stage

The Intensive stage of the BE WELL intervention is adapted from the Group Lifestyle Balance (GLB) program™ [66]. The GLB program is based on the highly successful Diabetes Prevention Program [57] and includes 12 weekly small group sessions. Each session follows a similar structure and includes five curriculum components: 1) measurement and recording of weight, 2) review of self-monitoring records and progress, 3) identification of personal barriers to weight loss and activity and potential solutions, 4) presentation of a new content area, and 5) goal setting and action plans for next week. In BE WELL, the GLB Manual of Operations will be closely followed, except for the addition of a food tasting activity as part of the check-in process and a 30-minute segment of physical activity demonstrations and practices at the end of each session. The food tasting activities are aimed at increasing participant experience with healthy food choices, encouraging them to try new foods that they might not normally try on their own, and stimulating a social, fun and engaging environment. The physical activity demonstrations and practices are aimed at increasing participant awareness of physical activity intensity, experiencing various moderate-intensity activities that are safe and that they can easily incorporate into their daily lives, and increasing participant confidence. As part of these supervised exercises, participants will learn how to recognize exercise-induced bronchospasm based on symptoms and peak flow meter readings and the appropriate prophylaxis and treatment. In BE WELL, participants will be given a pedometer and start using it to record their daily steps in week 1, as opposed to starting this in week 10 as in the original GLB program. Furthermore, BE WELL participants will attend an additional group session focusing on the latest evidence that came out after the GLB program on high-carbohydrate and high-fat/high-protein dietary approaches to weight loss to complement the program's emphasis on low-fat diets. The 13 group sessions of 90-120 minutes each will be delivered by a nutrition health educator and a fitness instructor over a 4-month period.

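### The primary model and the power statement make no allowance for clustering by session group in the WL arm; if that clustering exists, type I error exceeds 5%, and the claim that the power calculation is conservative is unsupported

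*Protocol article*

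**What the plan says.** **Delivery.** The Intensive Stage section states: "The 13 group sessions of 90-120 minutes each will be delivered by a nutrition health educator and a fitness instructor over a 4-month period". Table 3 lists these as in-person group contacts in months 1 to 4. Months 5 and 6 have one individual session each, and months 7 to 12 are individual and mainly by phone. The UC arm receives usual care, a pedometer, a scale and handouts, with no study groups. Group size is not given; the source programme is said only to be one that "includes 12 weekly small group sessions".

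**Allocation.** Individuals are randomized, not groups: "participants will be randomized in a 1:1 ratio to the WL or UC arm".

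**Model.** The Statistical analysis section describes a linear mixed model with "random effects caused by clustering of patients with physicians and, in turn, physicians within clinics, and by blocking of patients within medical centers". The residual term covers the correlation of repeated measures within a subject. No term for session group or interventionist is described. Equation 3 is not shown in the text available, so the model is read from this description.

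**Power.** The Sample Size section states: "A sample size of 324 is sufficient to detect an effect size of 0.4 between the WL and UC arms for 90% power at 5%" (two-sided alpha), "assuming up to a 20% loss to 12-month follow-up (or an end-of-the-study sample size of 259"). On method: "The power estimate was calculated based on an independent t-test using simplified assumptions". It then adds: "Note that the t-test calculation is conservative because it does not account for variance reduction due to adjustment for repeated measures", and cites the close balance of the arms as a second favourable factor.

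**The concern.** Physicians, clinics and randomization blocks exist before treatment and contain patients of both arms. Under individual randomization, similarity within them is largely common to WL and UC and drops out of the comparison. The session group is different: treatment creates it, and only in WL. Any effect shared by its members adds variance to the WL mean that a model without a group term does not see.

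The article does more than stay silent. It says which clusters are modelled, and it makes a positive claim about the direction of the power approximation. The claim counts the factors that help and leaves out the one feature of the design that can hurt.

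At stake is the standard error of the primary contrast on 12-month ACQ. The article applies the same analysis strategy to the secondary outcomes. An understated standard error leans toward declaring a benefit.

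**Working it through.** **Inputs from the article:** d = 0.4; 324 randomized 1:1; 20% loss, so 324 × 0.8 = 259 analysed, or 129.5 per arm; two-sided alpha 0.05; five recruitment cohorts.

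**Inputs assumed, because the article does not give them:** m, the completers per WL session group, and ICC, the within-group correlation of 12-month ACQ in WL. The main range is m = 6 to 16 and ICC = 0.01 to 0.05. One WL group per cohort would give m of about 130/5 = 26, shown as an extreme.

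**1. The plan's own figure.** With unit variance, SE = √(2/129.5) = 0.1243. Power = Φ(0.4/0.1243 − 1.96) = 89.6%; with the noncentral t it is 89.4%. The stated 90% reproduces, with no design effect in it.

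**2. WL-only clustering.** Total variance is held at 1 in each arm.
- Design effect in WL: DE = 1 + (m − 1) × ICC
- True variance of the contrast: (1 + DE)/129.5; the model without a group term works with 2/129.5
- Variance ratio: R = (1 + DE)/2
- Actual type I error: 2 × [1 − Φ(1.96/√R)]
- Power with the correct SE: Φ(0.4/√[(1 + DE)/129.5] − 1.96)

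Example, m = 10 and ICC = 0.05: DE = 1.45, R = 1.225, type I error = 2 × [1 − Φ(1.771)] = 7.7%, power = Φ(2.908 − 1.96) = 82.8%.

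| m | ICC | DE | Type I error | Unadjusted power |
|---|---|---|---|---|
| any | 0 | 1.00 | 5.0% | 89.6% |
| 6 | 0.01 | 1.05 | 5.3% | 88.9% |
| 6 | 0.05 | 1.25 | 6.5% | 85.9% |
| 10 | 0.01 | 1.09 | 5.5% | 88.3% |
| 10 | 0.02 | 1.18 | 6.0% | 86.9% |
| 10 | 0.05 | 1.45 | 7.7% | 82.8% |
| 16 | 0.01 | 1.15 | 5.9% | 87.4% |
| 16 | 0.05 | 1.75 | 9.5% | 78.4% |
| 26 | 0.01 | 1.25 | 6.5% | 85.9% |
| 26 | 0.05 | 2.25 | 12.4% | 71.4% |

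**3. Does the planned block effect repair it?** A simulation under no mean difference used 20,000 trials per setting, with one WL group and an equal number of UC participants in each block. At ICC 0.05:

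| Groups × m | t-test | With block intercept | Analysis of block-level differences |
|---|---|---|---|
| 13 × 10 | 7.8% | 8.0% | 5.1% |
| 10 × 13 | 8.7% | 8.9% | 5.2% |
| 5 × 26 | 12.8% | 13.1% | 5.0% |

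At ICC 0 all three methods gave about 5%. Monte Carlo error is about √(0.08 × 0.92/20,000) = 0.2 percentage points. The block intercept cancels from the contrast and leaves the inflation in place; an analysis that respects the groups holds 5%.

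**4. Can baseline adjustment offset this?** If adjustment multiplies all variance by 1 − ρ², power returns to its unclustered value when ρ = √(1 − 1/R). That gives ρ = 0.29 (m = 10, ICC 0.02), 0.43 (m = 10, ICC 0.05) and 0.52 (m = 16, ICC 0.05). The variance ratio R is unchanged, so type I error is too. If baseline explains none of the group variance, the m = 10, ICC 0.05 case needs (1.45 − ρ²) + (1 − ρ²) = 2, so ρ = 0.47. The ratio then rises to 2/(2 × 0.775) = 1.29, and type I error to 8.4%.

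**The case against.** **The ICC may be small.** Group contact ends in month 4, the primary endpoint is at month 12, and contact in between is individual. The Treatment Fidelity section standardizes delivery with checklists and a 10% audit. At ICC 0.01 and m = 10, type I error is 5.5%, which is close to negligible. This stands, and it is why the point is conditional. It does not justify fixing the ICC at exactly zero, as the described model does. The sessions are built around shared progress review and a social setting, Table 3 allows small-group visits again in months 7 to 12, and the article itself plans for interventionist drift.

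**If the sessions change nobody's ACQ, they create no group effect.** This is correct: under that strict null the error stays at 5%. The inflation concerns the null of no average effect, with group effects that vary around zero. The same understated standard error also narrows the confidence interval when the effect is real. At m = 10 and ICC 0.05, a nominal 95% interval covers about 100 − 7.7 = 92.3%.

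**Power is not shown to be below 90%.** A reader might infer from the table that the trial is underpowered. The documents do not support that. The planned model adjusts for baseline ACQ and covariates, and modest correlations would restore about 90% power (step 4). For the same reason no single replacement power figure can be given.

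**A condensed article leaves detail to a fuller plan.** This is fair for degrees of freedom and covariance structure. It does not cover the choice of which clusters to model or the claim of conservatism, both of which the article states. If Equation 3 allows the block effect to differ by arm, the description does not say so.

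**Blinding.** The Randomization and Blinding section keeps analysts on anonymous arm labels, and a WL-only term could reveal the arm. This is a real cost, dealt with in the fix.

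**Conclusion.** The concern holds in conditional form. As described, the primary model and the power calculation ignore clustering by WL session group. If the session-group ICC for 12-month ACQ is above 0, type I error is above 5%, and the block effect does not correct it. Over the assumed range (6 to 16 completers per group, ICC 0.01 to 0.05), type I error is about 5.3% to 9.5%, and 12.4% in the extreme case of one group per cohort at ICC 0.05. Unadjusted t-test power over the main range is about 89% to 78%.

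Two stronger readings go too far. That type I error *is* above 5% cannot be said, because neither ICC nor group size is in the article. That power *is* overstated cannot be said either, because baseline adjustment may make up the loss. The supported conclusion on power is that conservatism is asserted without weighing the one factor that works against it.

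**What to change.** 1. Record each WL participant's session group as assigned. Class attendance is already logged as a process measure, so this needs one more field.
2. Add to the primary model a random effect for session group that applies in WL only (a partially nested model), with small-sample degrees of freedom such as Kenward-Roger or Satterthwaite. Carry it to the secondary outcomes that use the same model.
3. Protect analyst blinding with coded group identifiers, for example a singleton code for each UC participant. Because cluster sizes could still show which arm is grouped, the safer course is to write and lock the code under blinding and fit this model at final unblinding.
4. Remove the unqualified statement that the t-test is conservative. Report power for d = 0.4 over a stated range of ICC and group size, with and without credit for baseline adjustment.

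The costs are somewhat wider confidence intervals, a less favourable power statement before baseline credit, and a variance component that is imprecisely estimated if there are few groups. If the ICC proves negligible, little is lost.
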